## Abstract

**Background:**

Social franchising is the fastest growing market-based approach to organising and improving the quality of care in the private sector of low- and middle-income countries, but there is limited evidence on its impact and cost-effectiveness. The “Sky” social franchise model was introduced in the Indian state of Uttar Pradesh in late 2013.

**Methods/design:**

Difference-in-difference methods will be used to estimate the impact of the social franchise programme on the quality and coverage of health services along the continuum of care for reproductive, maternal and newborn health. Comparison clusters will be selected to be as similar as possible to intervention clusters using nearest neighbour matching methods. Two rounds of data will be collected from a household survey of 3600 women with a birth in the last 2 years and a survey of 450 health providers in the same localities. To capture the full range of effects, 59 study outcomes have been specified and then grouped into conceptually similar domains. Methods to account for multiple inferences will be used based on the pre-specified grouping of outcomes. A process evaluation will seek to understand the scale of the social franchise network, the extent to which various components of the programme are implemented and how impacts are achieved. An economic evaluation will measure the costs of setting up, maintaining and running the social franchise as well as the cost-effectiveness and financial sustainability of the programme.

**Discussion:**

There is a dearth of evidence demonstrating whether market-based approaches such as social franchising can improve care in the private sector. This evaluation will provide rigorous evidence on whether an innovative model of social franchising can contribute to better population health in a low-income setting.

**Electronic supplementary material:**

The online version of this article (doi:10.1186/s13012-015-0269-2) contains supplementary material, which is available to authorized users.

## Background

Over the past few decades, India’s maternal mortality ratio has declined substantially from 437 deaths per 100,000 live births in 1992–1993 to 178 deaths per 100,000 live births in 2010–2012 [1, 2]. Despite these improvements, the current state of maternal and child health in India requires urgent attention. India remains the largest contributor to the global burden of maternal deaths, accounting for nearly a quarter of all maternal deaths worldwide [3]. One of the most high profile responses of the Government of India has been to encourage facility births by providing cash incentives to women through the Janani Suraksha Yojana (JSY) scheme. Studies show that the programme has been effective in increasing utilisation of government maternal health services even if the evidence on mortality is contested [4, 5]. However, there are concerns about the public sector and its capacity to meet the increased demand for institutional deliveries. Whether the resources of the private sector should be harnessed to improve maternal health, and other aspects of health, is at the forefront of ongoing debates [6].

India’s private health sector is extensive and incredibly diverse. It ranges from sophisticated tertiary hospitals providing medical care of an international standard to unqualified rural health providers and alternative systems of medicine. The majority of registered doctors work in the private sector, and it is often the first point of contact for a substantial proportion of the population [7–9]. In Uttar Pradesh, the setting of this study, 31 % of all facility births are in the private sector [10]. Although no worse than the public sector, studies of the private sector in India document poor quality of primary health care and potentially harmful practices [11].

Despite widespread consensus on the growing presence and role of the private sector in low- and middle-income countries, there is limited evidence on the most effective strategies to improve the quality of services [12, 13]. Regulating the quality of the private sector given its size and diversity has proved enormously challenging for the government, and alternative strategies to raise standards must be sought. Innovative approaches currently being used to tackle and institutionalise quality improvement include accreditation [14], contracting out clinical services [15], vouchers [16], and social franchising [17].

Social franchising is the fastest growing market-based approach to organising and improving the quality of care in the private sector in low- and middle-income countries [18]. In 2013, 83 franchises were largely operating in Sub-Saharan Africa and Asia reaching nearly 20 million patients [19]. Social franchises are networks of private providers, operating under contracts with a common agency and providing standardised products and services under a single brand. Social franchises typically have five programmatic goals: quality, health impact, equity, cost-effectiveness and market expansion. Franchise models that link with and encourage referrals between the public and private sector may help reduce health market fragmentation and improve quality of care. Common franchise elements include demand- and supply-side components relating to contract design, training, supervision, branding and advertising.

This study protocol describes the methods to be used in an evaluation of the Sky social franchising model in Uttar Pradesh. The aim of the social franchise model is to increase access to and use of basic obstetric care, emergency obstetric care and family planning services. The evaluation will draw on quantitative and qualitative methods to address three study objectives: (1) to estimate the impact of the social franchising model on the quality and coverage of health services along the continuum of care for reproductive, maternal and newborn health; (2) to understand the scale of the social franchise network, the extent to which various components of the programme are implemented and how impacts are achieved; and (3) to establish the cost-effectiveness and financial sustainability of the programme.

### Evidence on social franchising

Our review of the evidence draws on three recent systematic reviews of social franchising in health [17, 18, 20]. The majority of the social franchise programmes focus on reproductive services and family planning products, which together account for a large proportion of the literature on the topic [18, 20]. Before examining the empirical evidence, it is important to note that the methodological rigour of studies on social franchising in low- and middle-income countries is poor. This is demonstrated by the fact that the most thorough review of social franchising, published in the Cochrane library, found no studies eligible for inclusion despite the fact that inclusion criteria were broad enough to permit a range of quasi-experimental methods [17]. None of the reviews uncovered any evidence on the health impact or cost-effectiveness of social franchising.

In a second review, studies of clinical social franchise programmes were included if they provided data on at least one outcome related to quality, health impact, equity, cost-effectiveness and market expansion [18]. Quasi-experimental and qualitative studies were not excluded. The authors included 23 studies whose overall quality was regarded as low. The review found limited and mixed evidence on impact. Social franchising was found to increase client volume and service utilisation, but there was no evidence on the ability of social franchising to expand the availability of health services in currently underserved areas. Over half of the studies measured some aspect of quality but always in relation to family planning services and rarely in a comprehensive manner. A study in Pakistan and Ethiopia found that franchises were of equivalent or lower quality than public clinics but higher quality than non-franchised private providers. In Nepal, both franchised and non-franchised clinics showed similarly poor facility quality.

A third review of social franchising included 15 studies that examined the relationship between franchising and outcomes [20]. Around half focused on quality and utilisation, and a few considered results for providers, client loyalty, client volumes and efficiency. Reproductive health/family planning services research were well represented; other sectors investigated were pharmacy and tuberculosis care. The authors found that franchising is predominantly positively associated with client volumes, physical accessibility and some types of quality, but findings regarding utilisation, customer loyalty and efficiency were mixed. The methodological quality of studies was found to be poor.

In summary, the current scientific evidence and body of knowledge on the impact of social franchising, or on the sustainability of social franchising as a long-term alternative to the public sector, suggest that generalisations about the value of franchising are difficult to make. There is some evidence on the ability of clinical social franchising to increase patient volume and some aspects of quality of care. However, in general, the quality of evidence is sufficiently poor and variation in the types of social franchising models tested so wide that no firm conclusions can be drawn about whether and how social franchises affect service delivery.

### Social franchise model

The Sky franchise network includes providers at various levels. SkyCare is the lowest level of the network and consists of informal rural health providers who are typically medically unqualified. SkyCare providers pay a franchise joining fee to the franchisor and receive signage, posters, training manuals and the ability to phone into a central medical facility. The franchisor maintains the central medical facility by employing qualified doctors to conduct remote medical consultations. SkyCare franchisees are given financial incentives by the network to make antenatal care referrals to SkyHealth franchisees. The second level of the network is SkyHealth. These providers are typically qualified traditional medical practitioners trained to provide Ayurvedic, Yoga & Naturopathy, Unani, Siddha and Homoeopathic care (AYUSH). SkyHealth offers telemedicine services and receive financial incentives for completing three antenatal care consultations with a client. At the highest level, nine franchised clinics and three franchisor-owned clinics are staffed by physicians to provide safe delivery and emergency obstetric care.

The programme provides clinical training to private and public sector health providers. The franchisor trains SkyCare in how to conduct mobile phone consultations. SkyHealth is trained to provide antenatal care, recognise and stabilise pregnancy complications, facilitate timely referrals and provide family planning methods and postpartum contraception counselling. Providers from franchised clinics receive training on national and international guidelines to provide emergency obstetric care, general family planning and postpartum intrauterine devices. Public sector providers with the remit of dealing with emergency obstetric cases also receive clinical training in order to manage linkages and referrals from the private sector. Training in the public sector extends to Accredited Social Health Activist (ASHA) working at the community level. An additional file details the training programme by type of provider [see Additional file 1].

The social franchise model takes a total market approach in the sense that it seeks to develop closer links to, and strengthening of, the public sector. The major components of the programme are summarised in Table 1, using an adaptation of the Centre for Health Market Innovations framework for characterising health programmes [21]. Components fall into five major approaches: organising delivery, regulating performance, financing care, changing behaviours and enhancing processes. These approaches include both demand- and supply-side activities to influence health care-seeking behaviours and the quality of healthcare provision. Demand-side activities include incentivising rural health providers for referrals, brand creation, price subsidies for clients below the poverty line and advertising of franchise services. A major demand-side activity of the programme is social marketing, in which the franchisor distributes their own branded medicines—SkyMeds—via a network of shops, pharmacies and franchisees. SkyCare and SkyHealth providers are encouraged to sell SkyMeds, though it is optional. Supply-side activities include clinical training for providers, telemedicine and mobile technologies and the introduction of innovations such as the non-pneumatic anti-shock garment to stabilise women with heavy bleeding in both private and government facilities.

**Table 1 Tab1:** Components of the social franchising programme

Organising delivery	Programmes that reduce fragmentation and informality of health care delivery and that may enable financing, regulation, training and new business models	
Franchise	A group of providers that operates under the same brand but where outlets are operator-owned and services are standardised by a central franchisor	SkyCare/SkyHealth (stand-alone franchises); franchise clinic/franchise diagnostic (fractional franchises)
Chain	A group of providers that operates under the same brand but where operators are paid employees of a sponsoring organisation	Three franchisor-owned clinics (also called mini-clinics)
Network	A group of providers that are loosely joined to deliver services to specific population groups. Each provider is a separate entity and retains its own branding. Membership in the network may entitle the provider to payments, patient volume, central services or training	Franchisees are linked to a network of shops selling drugs which receive socially marketed products
Regulating performance	Programmes that set standards and enforce or incentivize higher quality care or increased access for target populations	
Quality enforcement/monitoring	Programmes that mandate specific clinical practice guidelines, and/or monitor providers over time to ensure quality	Monitoring and supervision of quality standards in franchisees, exit surveys and encourage feedback from competitors
Price regulation	Programmes or regulations that specify prices that must be charged to users for services	Fixed prices for below the poverty line clients at Sky Centres; fixed prices for franchised services at franchised clinics
Financing care	Programmes that mobilise funds for health care and align provider incentives to increase access for targeted groups of patients or to support select health interventions	
Links to government health financing mechanisms	Initiatives that link private providers to existing government health financing mechanisms that can contract and reimburse private providers for care provided to specified patient groups	Plan to facilitate linking franchisees and beneficiaries to government cash incentive and insurance schemes. Training of community health workers to link with government schemes
Cross subsidisation	Programmes that charge full-fees for services to patients that are able to afford them and use the profits to subsidise services for the poor	Subsidies for telemedicine for clients below the poverty line off-set to some degree by franchise fee paid per client above the poverty line
Changing behaviours	Programmes designed to change the behaviour of individuals involved in health care transactions	
Social marketing	Programmes that aim to change consumer care-seeking behaviours through marketing/advertisement techniques, with or without a branded and/or subsidised product	Branding, advertising, SMS messages, provision of SkyMeds
Community health workers	Programmes that use community health workers to generate demand for products or services	Government community health workers refer women to public and franchised facilities
Provider training	Programmes that seek to improve the quality and/or efficiency of services by training health care workers and/or building the internal capacity of organisations	Training of SkyCentre staff, franchise clinic staff, community health workers and public sector staff. Sky centre staff also trained on telemedicine technology
Other health awareness/education	Programmes that create social awareness and educate the public about specific health topics such as disease prevention and treatment, healthy behaviours, correct use of pharmaceuticals, etc.	Community system to give health messages
Organising delivery	Programmes that reduce fragmentation and informality of health care delivery and that may enable financing, regulation, training and new business models	
Enhancing processes	Processes, technologies, or products that facilitate increased efficiency, lower costs, higher quality, and/or improved access	
Information and communications technology	Programmes that utilise technology to enable remotely delivered care, communication and exchange of medical information (e.g. telemedicine, call centre, cell phone technology, biometric system, etc.).	Cell phone/smartphone/tablet/telemedicine services through franchisees, including remote diagnostics
Innovative operational processes	Programmes that improve quality, reduce costs or enhance efficiency of services through new business or care processes (e.g. high-volume/low-cost operational models, process standardization).	Telemedicine; getting auxiliary nurse midwives to insert intrauterine devices in rural areas
Mobile health	Programmes that utilise various models of transportation to deliver services to rural and remote populations. (e.g. ambulance services, health worker transport, travelling clinics/products, etc.)	May have Sky ambulance and link to “108” ambulance
Supply chain enhancements	Programmes that reduce costs and improve efficiency of supply chains that move medical products from manufacturer to retailer	Last mile outriders (SkyMeds and diagnostics)
Innovative medical products and equipment	Programmes that design, manufacture and sell new products such as rapid testing kits, nutritional supplements or other medical supplies that reduce costs, improve quality or enable remote care	Non-pneumatic anti-shock garment; stabilisation procedures at lower levels; remote diagnostics; safe delivery kits

### Theory of change

A theory of change for the social franchising programme was developed in collaboration with the implementing franchisor in December 2013. The results chain of the Sky social franchise model was used for this purpose and is detailed in an additional file [see Additional file 2]. It shows the sequence of inputs, activities and outputs that are expected to improve outcomes. The results chain is clearly a naïve simplification of reality, but it nevertheless provides a useful framework for understanding how the programme is intended to work as originally designed.

We highlight here the most important pathways that are critical to generating the intended impacts. First, health providers are willing to join the network and expand the range of services they offer to include reproductive and maternal health services. Second, the branding of social franchisees provides a signal of quality that increases patient demand for their services. Third, the monitoring of standards and the prospect of better business performance encourage health providers to improve their quality of care. Fourth, training and the provision of IT such as telemedicine increase skills and knowledge, ultimately leading to better quality of care and appropriate referrals.

Several key assumptions underpin the programme’s success. All else equal, basic economic theory suggests that increasing the quality of a service will raise consumer demand. In healthcare, however, information problems are pervasive and patients may not in fact be able to evaluate the quality of care they received, at least in terms of aspects of care that matter for health [22–24]. The extrinsic incentives to improve quality may therefore not be strong. Another important assumption is that lack of provider knowledge and skills are binding constraints to delivering quality healthcare. The evidence here is somewhat mixed. A meta-analysis of studies in low- and middle-income countries shows that training has a modest effect on provider practice [25]. In India, the qualifications of the provider matter for quality but not as much as expected [26].

## Methods

### Study setting

Uttar Pradesh is India’s fourth largest and most populous state with approximately 199.8 million people living in 18 divisions and 75 districts. If Uttar Pradesh were a country, it would be the fifth largest in the world in terms of population. The three districts in which the social franchising network is located have a population of 8.1 million and vary considerably in terms of demographic and health indicators (see Additional file 3). Kanpur Nagar is predominant urban, with higher literacy and lower mortality than the state average. By contrast, Kannauj and Kanpur Dehat are more typical of the state as a whole. Largely rural, they have poor literacy and high rates of maternal and child mortality that are comparable with the less developed countries in the world.

Across the continuum of care, large discrepancies in maternal and child health indicators are observed between the three districts [see Additional file 3]. For example, coverage of at least three visits of antenatal care in Kanpur Nagar is the highest at 51 % compared to 15 and 32 % in Kannauj and Kanpur Dehat, respectively. Despite government schemes to improve rates of institutional births, 54 % of deliveries occur at home in Uttar Pradesh (57 % in Kannauj, 40 % in Kanpur Nagar and 52 % in Kanpur Dehat). Of the home deliveries, 11 %, 53 % and 29 % were conducted by skilled health personnel in Kannauj, Kanpur Nagar and Kanpur Dehat, respectively.

### Study design

The impact study is designed as a prospective controlled before and after study in which the comparison group comprises matched areas both within the intervention districts and in neighbouring districts where social franchising is not introduced. The overall design is shown in Fig. 1. The primary sampling unit for much of the data collection is a cluster, defined as a ward (urban) or a village (rural) according to the most recent census. The impact evaluation involves the selection of study clusters to form three arms. Group A contains clusters with a social franchisee in the three intervention districts. Group B comprises clusters with no social franchisee in the same three districts. Group C is taken from neighbouring districts that do not have any social franchise network operating within them.

**Fig. 1 Fig1:**
[figure not shown]
Study design and data collection

The selection of study areas was done 14 months after the first health providers were contracted at which time there were 50 SkyHealth and 343 SkyCare providers in the social franchise network. The selection of study clusters proceeds according to the following steps. First, we link every social franchisee to the census area in which it is located and select, at random, 60 intervention clusters (Group A). Second, we select similar controls by matching without replacement the intervention clusters to 60 comparison areas within the same three districts (Group B) [27]. As can be seen in Fig. 2, we impose a buffer zone of 0.5 km around intervention clusters to limit problems of contamination. We perform exact matching on district and urban residences and then within each strata, select pairs of clusters (nearest neighbour) with the smallest distance based on a Mahalanobis metric that is computed using census data on total population, % under 6 years, % females under 6 years, % literate females, % scheduled tribe, % scheduled caste, % cultivator and % “other” workers. Finally, we perform the same matching procedure to select 60 comparison areas in neighbouring districts (Group C).

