### Empirical analysis

The impact evaluation relies primarily on the household data. We use a difference-in-difference strategy to estimate impacts [34]. This involves a comparison of changes in the outcomes over time between the intervention and the comparison groups. The analysis exploits the longitudinal nature of the data generated by the recall period used in the two rounds of the household survey and information on the precise timing of the introduction of social franchising in each study area. Specifically, using individual level data, we regress each outcome on a dummy variable indicating whether social franchising has been introduced in the area at the time of birth, area fixed effects and quarter year fixed effects. Unadjusted estimates are reported as well as those that adjust for household characteristics. Controls for household characteristics include below the poverty line status, urban residence, religion, ethnicity, maternal education, parity, multiple birth and the recall period. We cluster the standard errors at the area level.

We test whether the social franchising model has an effect in two ways: the first analysis compares intervention areas with the two sets of comparison areas pooled together, and the second analysis compares the intervention areas with the comparison areas in adjoining districts without social franchising. The latter may arguably be less prone to selection bias since comparison areas in neighbouring districts are beyond the geographical reach of the project and may offer a more credible counterfactual. If the social franchising model is found to have an effect on any of the main outcomes, we conduct subgroup analyses with respect to below the poverty line status, maternal education and caste. Finally, to assess the so-called parallel trends assumption that underpins the difference-in-difference approach, we exploit the recall period in the household data to verify that trends in each of the outcomes are similar between the three study arms before the introduction of the social franchising model. Evidence of diverging pre-trends would be a cause for concern. Baseline outcomes and characteristics of women are also summarised for each study arm with continuous variables presented as mean (standard deviation) and categorical variables by frequencies (percentage). An additional file describes the empirical strategy of the impact evaluation in further detail [see Additional file 4].

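### As worded, the 0.5 km buffer protects Group B from the 60 sampled franchised clusters but not from franchised areas that were not sampled or that join later

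*Protocol article*

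**What the plan says.** Cluster selection is described in the protocol article under Methods, Study design.

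- **Network size at selection.** "there were 50 SkyHealth and 343 SkyCare providers in the social franchise network".
- **Group A.** The first step reads: "we link every social franchisee to the census area in which it is located and select, at random, 60 intervention clusters (Group A").
- **Group B.** The 60 intervention clusters are matched to 60 comparison areas in the same three districts. The stated condition is that "Group B comprises clusters with no social franchisee in the same three districts".
- **Buffer.** In the matching step, with a reference to Fig. 2, "we impose a buffer zone of 0.5 km around intervention clusters to limit problems of contamination".
- **Group C.** "Group C is taken from neighbouring districts that do not have any social franchise network operating within them". It is chosen by the same matching procedure, and no distance rule is mentioned either way.

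Under Empirical analysis, exposure is a dummy for whether franchising had been introduced in the woman's own area when she gave birth. Two contrasts are planned: Group A against Groups B and C pooled, and Group A against Group C alone. The second is preferred on selection grounds because "comparison areas in neighbouring districts are beyond the geographical reach of the project". The Study design section also expects some Group B clusters to gain a franchisee as the network grows.

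**The concern.** The buffer exists because the protocol accepts that being close to a franchisee can contaminate a comparison area. A franchisee in an undrawn area is no less a source of contamination than one in a drawn area. If the buffer surrounds the drawn areas alone, a Group B cluster can adjoin an undrawn franchised area and still qualify, since it need only have no franchisee of its own. Its births are then coded unexposed for the whole study. The same applies to a Group B cluster that gains a franchised neighbour after selection.

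Reach beyond a single village or ward is part of the programme. SkyCare providers are paid to refer women to SkyHealth providers, there are about seven of the former to one of the latter (343/50 = 6.9), and the process evaluation section speaks of SkyHealth catchment areas.

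Area fixed effects would absorb spillover that is constant over time. They would not absorb this, because the network starts within the window of births studied: the article counts on almost 12 months of pre-franchise births. Spillover would therefore begin part-way through, and the difference-in-difference estimate would treat it as background change in the comparison group.

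**Working it through.** **1. Which areas the buffer surrounds.** The term for intervention clusters occurs three times in sequence: in the random draw of 60, in the matching of those clusters to 60 Group B areas, and in the buffer sentence. In the second use it can mean only the 60. The plain reading carries that meaning into the third.

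**2. Whether undrawn franchised areas existed.**

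- Franchisees: 50 + 343 = 393.
- For none to be undrawn, all 393 would have to sit in 60 areas: 393/60 = 6.55 per area. A random draw of 60 would then also have had nothing to choose from.
- With A distinct franchised areas, the undrawn share is 1 − 60/A. A is not stated. It is at most 393 for these two provider types.

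| Franchisees per area (assumed) | A | Undrawn share |
|---|---|---|
| 1 | 393 | 84.7% (maximum) |
| 1.5 | 262 | 77% |
| 2 | 196 | 69% |
| 3 | 131 | 54% |
| 4 | 98 | 39% |

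**3. The plan's own sample size.** Inputs from Sample size calculations: p0 = 0.50, p1 = 0.58, m = 20 women per cluster, coefficient of variation k = 0.2, 80% power, 5% significance (taken as two-sided; the article does not say). The unmatched cluster formula for proportions is

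c = 1 + (1.960 + 0.842)² × [p0(1 − p0)/m + p1(1 − p1)/m + k²(p0² + p1²)] / (p1 − p0)²

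The bracket is 0.01250 + 0.01218 + 0.02346 = 0.04814. Then c = 1 + 7.849 × 0.04814/0.0064 = 60.03, against 60 stated. The figure reproduces, with power 0.800.

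**4. What spillover would do to the pooled contrast.** The article gives no spillover figure, so this is an illustration over an assumed range. Let f be the average fraction of the programme effect received across all Group B births, that is, the share of births near a franchisee multiplied by the fraction of the effect those births receive. Group B supplies 60 of 120 comparison clusters, so it is given half the weight.

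Pooled contrast = 8 × (1 − f/2) points. Power comes from the formula in step 3, with p0 raised by 0.08 × f/2 and 60 clusters per group.

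| f (assumed) | Pooled contrast | Power |
|---|---|---|
| 0 | 8.0 points | 0.800 |
| 0.10 | 7.6 points | 0.757 |
| 0.25 | 7.0 points | 0.685 |
| 0.50 | 6.0 points | 0.549 |

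These powers are on the article's simple endline basis of 60 against 60. The real analysis has more comparison clusters, two rounds and covariates, so the table shows the direction and rough scale of the loss and does not forecast power.

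**5. The other planned contrast.** Group A against Group C alone contains no Group B births, so spillover into Group B changes it by 0 points.

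**The case against.** The strongest reply is that the sentence can be read more widely. It does not contain the word only, and its reference to intervention clusters has no definite article, whereas the matching sentence has one. It could therefore mean the whole class of franchised clusters. All franchisees had already been linked to census areas, so a wider buffer was feasible. Fig. 2, cited for the buffer, is not available here. This stands as a reason for asking rather than asserting. It does not remove the point, because the wider reading is not what the paragraph's own sequence of terms suggests, and no sentence supplies it.

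A reader might also infer that some fixed large share, say four fifths, of franchised areas lay outside the buffer. The article counts providers, not areas. Four fifths would need about 300 distinct areas (60/0.20), which is not documented, and 69% to 39% follows at two to four franchisees per area.

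A reader might further infer that Group C has no buffer at all. That treats silence as absence. Group C is selected by the same procedure, lies in districts without the network, and could be exposed in this way only near a district border. Nothing in the article shows that any Group C cluster lies there.

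Finally, the analysis that drops Group B is already planned and described as possibly the more credible one. That is a real mitigation. It leaves the first-listed, pooled contrast unprotected.

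**Conclusion.** The point holds as a defect in a stated selection rule. On its plain wording the safeguard against contamination covers only part of the network, and Group B births beside an undrawn or later-joining franchisee would count as unexposed. The pooled contrast is the one at risk. The bias is towards zero if spillover acts in the same direction as the programme; a different kind of spillover could act otherwise.

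The size cannot be derived from the article. It gives neither the number of franchised areas, nor the total number of wards and villages, nor any measure of spillover. The undrawn share has an upper limit of 85%. The losses shown, 0.4 to 2.0 points of an 8-point effect, rest on assumed values of f from 0.10 to 0.50 and equal weight for Groups B and C. A direct contrast of Group A with Group B would lose twice as much, but no such contrast is planned. The Group C part is no more than a check worth making at district borders.

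**What to change.** 1. State whether the 0.5 km buffer was drawn around all franchised census areas or around the 60 sampled ones, and give the number of franchised areas at selection. If it covered all of them, correct the sentence; the check below is then needed mainly for later joiners.
2. For each Group B cluster and each birth date, compute the distance to the nearest area with an active franchisee, sampled or not. Do the same for Group C clusters near a district border. Measure distance in the way used for the buffer, and say what that was.
3. Report how many Group B and Group C clusters, and how many births, fall within 0.5 km.
4. Add a sensitivity analysis of the pooled contrast that excludes those births or codes them as a separate near-franchise category. Keep the planned analyses as they are.

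No new fieldwork is needed: every franchisee has been linked to its census area, and the timing of introduction comes from the franchisor's administrative data. Two limits apply. Outside the study clusters the provider survey cannot corroborate the start dates, and the link to census areas must be extended to franchisees who joined after selection. The price is fewer usable Group B clusters, some broken matched pairs and wider intervals, all confined to the sensitivity analysis. Separate coding keeps more of the data than exclusion and shows whether nearby births differ at all.
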